# Effect of mobile-based self-management application on stroke outcomes: a study protocol for triple blinded randomized controlled trial

**DOI:** 10.1186/s12911-022-02033-y

**Published:** 2022-11-11

**Keywords:** Mobile applications, Self-care, Stroke, Telemedicine, Telerehabilitation

## Abstract

**Background:**

Stroke is the main leading cause of long-term disabilities in the world. This protocol will be implemented for a study to evaluate the effects of an Android-based self-care application on patients with stroke.

**Methods:**

The first stage will include the development of an android-based application using JAVA programming language for developing the user interface and ASP.NET Core for developing Web server. The second stage will be conducted using triple blinded randomized clinical trial (RCT). The sample size will include 60 patients with recent stroke and partial paralysis of limbs, who will be divided into two groups of intervention and control through permuted block randomization method. Patients in both groups will receive usual medical care, but those in the intervention group will also use an Android-based application for a period of two months. Outcomes will be assessed using valid and reliable questionnaires.

**Discussion:**

The assessed outcomes will include stroke severity using National Institute of Health Stroke Scale (NIHSS) score, ability to perform activities of daily living using Barthel Index (BI) score, depression rate using Beck Depression Inventory (BDI-II) score, quality of life using EQ-5D-3L score, medication adherence using Modified Morisky Medication Adherence Scale (MMAS-8) score, patient satisfaction using Patient Satisfaction Questionnaire (PSQ) score and the number and type of complications in patients in two groups. These outcomes will be assessed at baseline, after two months and after three months from the beginning of the intervention. Intervention effects on the measured variables will also be evaluated using appropriate statistical tests based on the type of variable distribution. Potential consequences of the study might be the improvement of the measured variables in the intervention group compared to that of the control group. The expected results are that the intervention may significantly improve the status of the measured variables in the intervention group compared to that of the control group. If the outcomes of the intervention group do not change significantly compared to those of the control group, it can be due to different reasons. However, this can most likely be attributed to incorrect or insufficient use of the application by patients.

*Trial registration*: This protocol is registered in the Iranian registration of clinical trial (IRCT) on November 7, 2020 with the code IRCT20201015049037N1. URL: https://irct.ir/trial/51674

## Background

The incidence of stroke in 2017 (based on findings from 21 regions of the world) was 11.9 million cases, and the disease is the second leading cause of death worldwide and the main leading cause of long-term disabilities [1]. According to the World Health Organization (WHO), of the 56 million deaths that occur worldwide each year, 10.8% are due to stroke [2]. Stroke includes a group of pathological disorders of cerebral arteries characterized by decreased neurological and non-convulsive function due to cerebral ischemia or intracranial hemorrhage [3]. Stroke has a variety of consequences for patients [4] and stroke survivors usually experience a wide range of symptoms related to motor function, speech, swallowing, vision, sensation and perception, and their recovery can be slow and incomplete [5, 6]. These symptoms often lead to limited participation in home and community activities. Rehabilitation procedures for these people are often long-term and require a lot of resources. However, only half of survivors have access to rehabilitation services after discharge [7]. In a qualitative study, Anderson et al. [8] concluded that mobile-based applications could improve self-care in patients with chronic conditions. Other studies have shown the impacts of mobile-based training on improving stroke outcomes [9, 10]. An increasing number of Randomized Clinical Trials (RCTs) have evaluated the effectiveness of telerehabilitation interventions. Nevertheless, it is difficult to draw conclusions about the effects of these interventions since the type of interventions and comparisons performed vary greatly from study to study. Some studies have shown the effects of mobile-based applications on improving and enhancing some of the measured outcomes in patients after stroke [11–14] while other studies showed the use of these applications does not make a significant difference compared to usual care. [15, 16]. In addition, the results of a number of studies do not seem to be generalizable and might be at the risk of being biased, and accordingly more studies are needed to yield more definitive conclusions [7]. Therefore, in this study, we intend to first develop a mobile-based application and then solve its usability problems by expert-based usability evaluation. Finally, an interventional study will evaluate the effects of this application on patients with stroke. The effect assessment of the application will be done by focusing on the three main parts of the International Classification of Functioning, Disability and Health (ICF), namely the physical structure, individuals’ activities and social participation. To write this paper, the conventional SPIRIT (Standard Protocol Items: Recommendations for Interventional Trials) checklist and guidance on reporting e-health and m-health trials written by the CONSORT-EHEALTH (Consolidated Standards of Reporting Trials of Electronic and Mobile Health Applications and online Telehealth) group [17] were used.

## Methods

This RCT will be done in two stages. The first stage will include the development of an android-based application, with the second stage being the evaluation of the effects of this application on patients with stroke.

### Stage 1: application development

Application development will be based on the model presented by Chavez et al. in 2019 [18] (Fig. 1). This model is a combination of iterative and incremental models in system development. According to this model, software development will be done in three different phases, which include the following:Determining functional requirementsDesigning a low-fidelity prototype and evaluating its validityDesigning a high-fidelity prototype and evaluating its usability

**Fig. 1 Fig1:**
[figure not shown]
Method of software development

#### Determining functional requirements

In this phase, the functional requirements of the application will be determined. Functional requirements will be obtained through the following four methods:Selecting clinical guidelinesReviewing similar studies and applicationsNeeds assessment of patientsNeeds assessment and localization of requirements based on expert opinion

In this phase, based on the existing stroke self-care guidelines, one of the clinical guidelines approved by three neurologists will be selected at first and the functional requirements of this guideline will be extracted by researchers. Other functional requirements will also be extracted using a review study on applications done by researchers and similar studies. In this regard, some systematic review studies have been conducted [7, 19–22] which will also be reviewed by researchers. Needs assessment of patients will be done as the most important stakeholder group of the application. For this purpose, a semi-structured interview will be used with patients who have previously suffered from stroke and partial paralysis and have now partially recovered. Due to the specific conditions of the patients, the interview will be conducted in a maximum of 20 min, but the number of sessions can be increased to two or more sessions in order to assess patients’ needs. Sample interview questions are stated in Table 1. These patients are required to have at least a diploma and be able to work with a smartphone. Patient and caregiver interviews will continue until data saturation is reached and no new data should be produced in the interview. Samples will be selected by convenience sampling method. Finally, all these requirements will be prepared in the format of Lawshe approach [23] and will be given to the experts. At this stage, a questionnaire containing functional requirements and information content of the application will be given to neurologists, occupational therapists and physiotherapists for the purpose of localization. Delphi technique [24] will be used in this step. Moreover, for needs analysis, 15–21 neurologists, physiotherapists and occupational therapists who are faculty members of the country's medical universities and have at least three years of professional experience will be consulted. At this stage, for each requirement, the necessity, appropriateness, clarity and relevance will be evaluated and in terms of necessity (CVR: Content Validity Ratio), three levels (essential and useful, useful but unnecessary, non-useful) and in terms of appropriateness, clarity and relevance (CVI: Content Validity Index) four levels (from very high with a score of four to very low with a score of one) will be defined. Questions with a CVR score of higher than the base number (0.62 for ten individuals) based on Lawshe table will be approved and those with a CVR score of less than that will be removed. According to CVI, questions that have scores of higher than 0.79 will be approved and those with scores between 0.7 and 0.79 will be re-reviewed, corrected and returned to the experts and finally those with scores less than 0.7 will be rejected. This step will be repeated until the final validity of the questionnaire content is confirmed. The approved questionnaire will be provided to the experts in the next step and the experts' answers to the components of the questionnaire will be scored from 1 to 5 (very low = 1, low = 2, medium = 3, high = 4 and very high = 5) and then the average score of each item will be calculated. Minimum score for accepting each component will be considered as 3.75. If the score obtained for each component is between 2.5 to 3.74, that component will be modified and reviewed again. Components with a score of less than 2.5 will also be removed from the application content.

**Table 1 Tab1:** Example of questions for patient interviews

No	Question
Q1	During your illness, did you have any problems in doing activities of daily living (such as eating, going to the toilet, dressing, etc.)? Explain your problems
Q2	Did you suffer from complications caused by the disease such as bedsores, urinary and fecal incontinence, shoulder pain, falls, depression and other complications? Explain them and explain how you managed to improve them
Q3	Were you prescribed physiotherapy sessions? What exercises did you do during the physiotherapy treatment?
Q4	Did you have problems walking and maintaining your balance? Explain your problems
Q5	During your illness, did you feel the need to communicate with your doctor by phone? For what cases did you feel this need?
Q6	During your illness, did you feel the need for training to do some work? What training was needed more?
Q7	Did you need special training regarding prescribed drugs? (Knowing the side effects of drugs, changing the dosage of drugs, the duration of continuing to take the drug, or stopping the use of drugs, changing the type of drugs). Explain

The interview questions will not be limited to these questions and the interview will continue in depth until the patient's needs are acquired

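### The CVR removal threshold (0.62) is labelled for ten raters but the planned panel is 15–21; taken literally it is too strict by one to three votes

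*Protocol article*

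**What the plan says.** All of this is in the protocol article, Determining functional requirements.

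- Panel: "for needs analysis, 15–21 neurologists, physiotherapists and occupational therapists" will be consulted.
- Task: the next sentence reads "At this stage, for each requirement, the necessity, appropriateness, clarity and relevance will be evaluated". Necessity is rated on "three levels (essential and useful, useful but unnecessary, non-useful" and summarised as the content validity ratio (CVR).
- Approval: "Questions with a CVR score of higher than the base number (0.62 for ten individuals) based on Lawshe table will be approved".
- Removal: "those with a CVR score of less than that will be removed". By contrast, an item with a middling content validity index (0.7 to 0.79) is corrected and returned to the experts.
- Repetition: "This step will be repeated until the final validity of the questionnaire content is confirmed".
- Later round: the approved questionnaire is scored 1 to 5, with its own rule: "Components with a score of less than 2.5 will also be removed from the application content".

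The section Intervention then describes the tested app as holding all functional requirements that the experts approved.

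**The concern.** The minimum CVR depends on the number of raters, and the article shows this by attaching a rater number to its value. That number does not match the planned panel. The article's other expert groups are six prototype reviewers, five usability evaluators and groups of three neurologists. The only ten experts mentioned elsewhere belong to a cited validation of the satisfaction questionnaire.

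As the panel grows, a given CVR becomes less likely to arise by chance, so the minimum should fall. Keeping the ten-rater value for 15–21 raters makes the filter stricter than intended. An item that fails is removed, and nothing in the text says the later scoring round brings it back. At stake are the content of the app and a reader's ability to reproduce how that content was chosen.

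**Working it through.** **Inputs from the article:** cut-off 0.62, labelled for ten raters; panel N = 15 to 21; approval requires CVR above the cut-off.

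**Assumptions:** the top rating level counts as the essential vote; the table follows a two-sided 5% normal approximation against chance agreement of 50%. The article gives no alpha for the CVR and the table is not in the documents.

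**Formulas.** CVR = (n − N/2)/(N/2), with n the number of essential votes. Under chance, the critical CVR is 1.96/√N.

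**Reproducing the stated figure.** 1.96/√10 = 0.620, which matches 0.62. The one-sided version, 1.645/√10 = 0.520, does not.

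**Votes needed for N = 15 to 21.** The last two columns give the probability that an item passes when each rater independently calls it essential with probability 0.80 (an illustrative value): P(X ≥ votes needed), X ~ Binomial(N, 0.80).

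| N | 1.96/√N | Votes at fixed 0.62 | Votes at matched cut-off | Gap | Passes at 0.62 | Passes at matched |
|---|---|---|---|---|---|---|
| 15 | 0.506 | 13 (87%) | 12 (80%) | 1 | 0.40 | 0.65 |
| 16 | 0.490 | 13 (81%) | 12 (75%) | 1 | 0.60 | 0.80 |
| 17 | 0.475 | 14 (82%) | 13 (76%) | 1 | 0.55 | 0.76 |
| 18 | 0.462 | 15 (83%) | 14 (78%) | 1 | 0.50 | 0.72 |
| 19 | 0.450 | 16 (84%) | 14 (74%) | 2 | 0.46 | 0.84 |
| 20 | 0.438 | 17 (85%) | 15 (75%) | 2 | 0.41 | 0.80 |
| 21 | 0.428 | 18 (86%) | 15 (71%) | 3 | 0.37 | 0.89 |

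Example, N = 15: 12 votes give (12 − 7.5)/7.5 = 0.60, which fails 0.62 but passes 0.506; 13 votes give 0.733 and pass both.

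**How far this depends on the assumed table.**
- Exact binomial, one-sided 5%: 12, 12, 13, 13, 14, 15, 15 votes for N = 15 to 21. This differs from the matched column only at N = 18, and the gap is again one to three votes.
- Exact binomial, upper tail 2.5%: 12, 13, 13, 14, 15, 15, 16 votes. The gap is then zero at N = 16 and at most two.
- N = 21 is a near tie: 15 votes give 4.5/10.5 = 0.4286 against 0.4277. A table entry rounded up to 0.43 would require 16 votes, making the gap two and the pass probability 0.77 instead of 0.89.

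**Strongly endorsed items.** At 90% true agreement the pass probability under 0.62 is 0.82 to 0.93 across N = 15 to 21, against 0.94 to over 0.99 at the matched cut-off.

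**The case against.** The article never says that 0.62 will be applied to 15–21 raters. The rule refers to the base number in a table, and the parenthesis can be read as one example row, or as the number of respondents expected. A team holding the table would probably read the row for its own panel. This stands: a reader might infer that 0.62 is the operative cut-off, but the text does not settle it. The inconsistency remains on either reading, because if 0.62 is an example the operative value is unstated, and if it is operative it belongs to another panel size.

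A reader might also infer that components with clear majority support will be lost from the intervention. The documents do not support that. It would require literal use of 0.62, an item in the narrow affected band, and no rescue when the step is repeated. The CVR rule is also worded for questionnaire items, while removal from the application content is worded only under the later 1–5 rule. The method drops many majority-backed items even at the matched cut-off: 11 of 15 (73%) and 14 of 20 (70%) fail there too. Only the last one to three votes are due to the mismatch.

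Finally, this is content development before randomisation. Allocation, sample size, error rates and the comparison of the app as built are untouched. That stands in full. Nor is there a calculation error, since 0.62 is reproduced for ten raters.

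**Conclusion.** The point holds as an internal inconsistency of minor weight: the only CVR threshold printed does not fit the only panel described for that rating. If 0.62 is used literally, it demands one extra essential vote at N = 15–18, two at N = 19–20 and three at N = 21. With 80% true agreement and independent raters, that lowers an item's chance of surviving from 65–89% to 37–60% across the seven panel sizes.

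The direction, that 0.62 is too strict for more than ten raters, follows from the table's dependence on panel size. The exact vote gaps and percentages rest on the assumed 1.96/√N and would shift by about a vote under another construction. The documents do not show that any component would in fact be lost.

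**What to change.** In Determining functional requirements, replace the ten-rater value with the cited table's cut-off for the number of experts who actually return the form, and list the values for 15 to 21. If ten respondents are in fact expected, reconcile that with the stated 15–21. The figures worked out here are approximations and should not stand in for the table's entries. If the round is already complete, report the number of respondents and the cut-off used.

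The cost is one line of text. A few more items may go forward to the 1–5 scoring round, which still filters them.

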#### Development of low-fidelity interface

In this phase, based on the feedback and opinions received from experts in the previous step, first the items and how the application works as a conceptual model will be designed and then the low-fidelity user interface (how to display the content of the application and the relationship between humans and smartphones) on android platform will be developed using the appropriate programming language. Then, a primary prototype will be created and its validity will be evaluated. After implementing functional requirements on the prototype for checking validity, six experts will review the application and evaluate the extent to which functional requirements and goals are met by this prototype. These experts will include two neurologists, two physiotherapists and two occupational therapists with at least three years of specialized work experience in the field of treatment and rehabilitation of patients with stroke.

#### Development of high-fidelity interface

At this phase, based on the final version of the prototype obtained from the previous phase, the high-fidelity prototype will be developed by JAVA programming language. A web server will also be developed using ASP.NET Core. In order to evaluate the usability of the prototype, Cognitive Walkthrough (CW) method will be used based on the method proposed by Polson and Lewis [25]. By identifying and introducing tasks and actions and expressing them step by step, this method will enable those evaluators who have limited background knowledge about the system to identify usability problems properly [26]. For this purpose, a certain number of scenarios that represent the most important and frequent application functions will be identified in harmony with the opinion of three neurologists. For each scenario, the main objective, sub-objectives, sequence of steps to do the tasks and system responses will be prepared and approved by the researchers. Then, the program will be provided to the evaluators. Five individuals will be chosen to do the evaluation through non-probability quota sampling. Evaluators are required to have at least a master's degree in health information technology/management or medical informatics and have 2 years of professional experience in evaluating health information systems. They will independently perform the sequence of steps for each scenario through the program's user interface. Each evaluator will put themselves in the position of the patient and observe the program from the patient's point of view; in case of any problems in performing the task steps, it will be expressed by evaluators. This will happen at the presence of the researcher as an observer who will write the following items in data collection forms: evaluator's comments, questions and uncertainties, an explanation of the usability problem identified by the evaluator, location of the problem in the system and the time to perform each scenario. At the end of each evaluation process, each evaluator will review the list of the related problems and suggest any solutions to solve potential issues. Then, in a meeting, separate lists of evaluators will be compared and all of the identified problems will be put on the list of main problems. Next, any duplicate problems will be eliminated and the evaluators will be asked to assess the severity of the problems independently. This rating will be based on three criteria including frequency of the problem, impact of the problem and continuity of the problem. Scoring for each problem and criterion will be done in 5 degrees ranging from 0 (no problem) to 4 (severe problem). Then, the average of the identified problems will be calculated and relevant problems will be listed in order of intensity followed by feedback given to application designers. Also, in order to confirm usability of the application by users, the System Usability Scale (SUS) questionnaire will be used and will be distributed among 30 users who have previously had a stroke and have been working with the application for a week. This questionnaire will include 10 items (SUS01 to SUS10) with 5-point Likert scale and SUS score of 70 and above will be considered acceptable [27]. SUS scores will be calculated as follows:

SUS Score = 2.5 (20 + SUM (SUS01, SUS03, SUS05, SUS07, SUS09) − SUM (SUS02, SUS04, SUS06, SUS08, SUS10)). According to this formula, SUS01 means item number one in the questionnaire, and the list will continue. The validity and reliability of this questionnaire have been confirmed in previous studies and its average Cronbach's alpha coefficient was estimated to be 0.91 [28].

The results of users' comments will also be given to the designers. This step will be repeated until the application is approved by evaluators. The output of this phase will be the final version of the application, which will be ready to be implemented in a live environment. Support services including bug fixation, content changes and other application updates will be presented by system support staff/admin.

